**2.10 Sample Size Calculations:**

The primary outcome measure will be the proportion of patients who experience a respiratory exacerbation requiring intravenous antibiotics in the two treatment groups over the 24 week trial observation period. In our combination antibiotic susceptibility trial we enrolled and followed 251 patients with cystic fibrosis and randomized patients when they experienced a pulmonary exacerbation. Eighty-seven patients (35%) experienced an exacerbation requiring intravenous antibiotics within 24 weeks of enrolment47. Similarly, 32% of placebo-treated patients in The Australian hypertonic saline trial experienced a CF exacerbation requiring intravenous antibiotics within 24 weeks48. Finally, in the TOBI study 100 of 258 actively-treated patients (39%), and 135 of 262 placebo-treated patients (52%) experienced at least one pulmonary exacerbation requiring intravenous antibiotics over the 24-week trial49.

Additionally, data from the 2005 Toronto CF Data Registry suggests that of Canadian adult and pediatric patients who are chronically infected with aspergillus, 27% experienced at least one respiratory exacerbation during the first six months of 2005 which required hospital admission and/or home intravenous antibiotic therapy. According to the statistician ([name]) who administers the database this is likely an under-estimation of the true rate of exacerbations, since data on hospitalizations or home IV therapy can be missing or incomplete within the database.

Thus, based on data from the above-mentioned three recently completed studies, and based on the Toronto database data, we conservatively expect that 34% of placebo-treated patients in our trial will experience a pulmonary exacerbation requiring intravenous antibiotics over the 24 week duration of our trial. The Trial Investigators (4 Canadian CF physicians and 4 Australian CF physicians) determined that a 15% absolute difference in 24-week exacerbation rates between the two treatment groups would be the minimal clinically significant difference that would be important for the study to detect.

An MCID of 15% was decided upon for two reasons: 1) Data from Toronto suggests that at least 27% of pediatric and adult patients who are chronically infected with *A. fumigatus* experience a pulmonary exacerbation requiring IV antibiotics within a 24-week period, and that this risk is reduced to 11% in those who are not infected with Aspergillus (ie. a risk reduction of 16%). Thus a 15% absolute risk reduction might be expected if we can eliminate aspergillus infection in those study patients who are randomized to active anti-fungal treatment. 2) The study intervention is lengthy (24 weeks), expensive (approximately $16.00 per day for adults), and not without risk of side-effects. Therefore it was argued that unless a relatively large signal is seen, ie. unless the absolute risk reduction for exacerbation is at least 15%, then widespread implementation of the intervention would not be justified in the larger CF population. Assuming a binomial distribution for exacerbation rates, with a 15% absolute risk reduction between itraconazole vs. placebo, a two-sided alpha error of 0.05, and a beta error of 0.20, 148 patients per arm or 296 subjects in total are required. In order to allow for a 5% non-compliance rate (Lachin formula), a total sample size of 328 subjects is required.

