**2.12/2.13 Compliance and Losses to Follow-up**

The patient’s treating physicians will be instructed not to prescribe anti-fungal antibiotics to enrolled study patients. However, if a patient’s physician insists that the patient must be started on an anti-fungal agent during the study period, then the study medication will be stopped (to avoid potential over-dosage). The patient will continue to be followed for the duration of the study period and results will be analysed according to the intention-to-treat principle. Premature discontinuation of study medication, for reasons of adverse effects or lack of efficacy, will be assessed as a secondary outcome.

Based on previous trials, we expect that 5-10% of participants will prematurely discontinue study medication but continue in the study, and that less than 5% of patients will withdraw from the study and be lost to follow-up. Losses to follow-up are rare in CF trials since patients are all followed in a central CF clinic. For instance, in our combination antibiotic susceptibility trial there were no losses to follow-up despite a 4.5 year study duration47. Patient compliance will be assessed by assessing serum itraconazole levels at 12 and 24 weeks. Patients who have detectable blood levels of itraconazole at 12 and 24 weeks will be judged to have been compliant. Patients who are non-compliant will still be included in the primary intention-to-treat analysis.

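### Section 2.10 sizes the trial for 5% non-compliance alone, while section 2.12/2.13 expects 5-10% discontinuation plus some loss to follow-up, so the stated 80% power holds only at the favourable end of the protocol's own range

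*Protocol*

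**What the plan says.** Section 2.10 defines the endpoint for sizing as a binary one: "The primary outcome measure will be the proportion of patients who experience a respiratory exacerbation requiring intravenous antibiotics in the two treatment groups". The control rate is given as "we conservatively expect that 34% of placebo-treated patients in our trial will experience a pulmonary exacerbation requiring intravenous antibiotics". The target is set "with a 15% absolute risk reduction between itraconazole vs. placebo, a two-sided alpha error of 0.05, and a beta error of 0.20", which leads to "148 patients per arm or 296 subjects in total are required". The only allowance beyond that base is: "In order to allow for a 5% non-compliance rate (Lachin formula), a total sample size of 328 subjects is required".

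Section 2.12/2.13 sets out what the investigators expect in conduct, based on previous trials. On treatment discontinuation: "we expect that 5-10% of participants will prematurely discontinue study medication but continue in the study". On loss, as a separate item: "less than 5% of patients will withdraw from the study and be lost to follow-up". It then confirms how non-adherent patients are handled: "Patients who are non-compliant will still be included in the primary intention-to-treat analysis".

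Two further inputs bear on power. Section 2.14 names an unadjusted Fisher's exact test as the principal analysis. Section 2.16 sets the final significance level at 0.048, after one interim look at 0.005.

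**The concern.** Both sections describe the same trial, but they do not use the same attrition. Patients who stop drug and stay in the intention-to-treat comparison pull the two observed proportions together. Patients who are lost reduce the number of outcomes. The inflation in section 2.10 covers the first effect at the bottom of the range given in section 2.12/2.13 and does not cover the second. Nothing in the protocol explains the difference.

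The 15-point difference is the one the investigators call the minimum worth detecting, so the type II error attached to it matters if the result is null. A reader would be told that error was 20%, although the protocol's own expectations put it at 20% only under the most favourable combination.

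**Working it through.** **Inputs.** Placebo 34%, itraconazole 19% (34% minus 15 points), two-sided alpha 0.05, power 80%, 148 per arm, total 328 (section 2.10); 5-10% discontinuation and under 5% loss (section 2.12/2.13); Fisher's exact test (section 2.14); final alpha 0.048 (section 2.16).

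**Step 1: reproduce the base.** With p̄ = (0.34 + 0.19)/2 = 0.265 and d = 0.15, the usual two-proportion formula is

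n = [1.96·√(2·0.265·0.735) + 0.842·√(0.34·0.66 + 0.19·0.81)]² / 0.15² = 134.7 per arm.

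The continuity correction gives (n/4)·[1 + √(1 + 4/(n·d))]² = 147.7, that is 148 per arm or 296 in total. This matches. Exact two-sided Fisher power at 148 per arm is 80.6%, so the continuity correction is what Fisher's test needs and leaves no real reserve.

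**Step 2: reproduce the inflation.** N/(1 − R)² with R = 0.05 is 296/0.9025 = 327.98, that is 328. This matches, and it leaves nothing over for loss to follow-up.

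**Step 3: put in the rates of section 2.12/2.13.** The assumption behind this inflation is that stoppers have the placebo risk. The itraconazole proportion then becomes 0.19 + R·0.15, which is 0.1975 at R = 5%, 0.20125 at 7.5% and 0.205 at 10%. For loss, I assume that lost patients contribute no outcome: 164 × 0.95 = 155.8, so 156 per arm at 5%, and 164 × 0.975 = 159.9, so 160 per arm at 2.5%. Exact Fisher power, by full enumeration:

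| Stopping | Lost | n per arm | Power, alpha 0.05 | Power, alpha 0.048 |
|---|---|---|---|---|
| 5% | 0% | 164 | 80.4% | 79.7% |
| 5% | 5% | 156 | 78.1% | 77.7% |
| 7.5% | 0% | 164 | 78.0% | 77.2% |
| 7.5% | 2.5% | 160 | 76.8% | 76.1% |
| 10% | 0% | 164 | 75.4% | 74.5% |
| 10% | 5% | 156 | 73.0% | 72.5% |

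The first row reproduces the plan. The 0.048 column treats the final test on its own and ignores the small chance of stopping at the interim look.

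**Step 4: scale in patients.** By the protocol's own method, 10% stopping would give 296/0.90² = 365.4, about 366 in total. Adding 5% loss gives 365.4/0.95 = 384.7, or 386 when each arm is rounded up. These totals only show the size of the gap; they are not a proposal to enlarge the trial.

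**The case against.** The strongest reply is that the lower figures stack unfavourable assumptions.

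- **Loss is a ceiling.** Section 2.12/2.13 says less than 5% and calls losses rare, and sections 2.11 and 2.12/2.13 both report none in the group's earlier trial. The 73.0% figure is therefore a worst case and not the expected one. This stands. Loss is not needed for a shortfall, however: 10% stopping alone gives 75.4%.
- **Lost patients may not be dropped.** The protocol does not say how they enter the primary analysis; removing them is my assumption. This stands too.
- **Full reversion to placebo risk is pessimistic.** A patient may stop late, or after an event, and section 2.12/2.13 has study drug stopped when a physician starts an antifungal, so some stoppers would be on active treatment. If stoppers kept half the benefit on average (an assumption), 10% stopping would dilute the effect as 5% full reversion does: 80.4% with no loss and 78.1% with 5% loss. This stands as a limit on the size. But section 2.10 chose an inflation that assumes no retained benefit, and the check only carries that choice over to the other section's rates.
- **The alpha of 0.048 is a side issue.** It costs under one point. Agreed.

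A reader might infer that 328 is a miscalculation, or that the trial cannot reach 80% power on its own assumptions. The documents support neither. Both 296 and 328 reproduce exactly, and 5% stopping with no loss lies inside the stated range and gives 80.4%.

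**Conclusion.** The inconsistency is real and of moderate weight. It concerns assumptions that differ between two sections, not arithmetic. On the rates in section 2.12/2.13, power for 34% versus 19% runs from 80.4% down to 73.0% at alpha 0.05 (79.7% to 72.5% at 0.048), so type II error lies between about 20% and about 27%. The middle of the discontinuation range with no loss gives 78.0%.

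These figures rest on stoppers having the placebo risk and lost patients contributing no outcome. Retained benefit would narrow the gap. Type I error, the validity of the estimate and the conduct of the trial are unaffected. It would go too far to treat this as a defect that undermines the trial; what needs correcting is a power statement that is true only at the favourable end.

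**What to change.** Restate section 2.10 on the assumptions of section 2.12/2.13. Suggested wording:

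*With 328 patients, Fisher's exact test at a final two-sided alpha of 0.048, 5-10% discontinuation of study drug and up to 5% loss to follow-up, power to detect 34% versus 19% is about 72-80%, with 80% reached only at the favourable end. This assumes that patients who discontinue have the placebo risk and that patients lost to follow-up contribute no outcome.*

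If the sponsor holds that 5% is the right planning figure, the alternative is to justify it in section 2.10 and align section 2.12/2.13 with it.

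The cost is one paragraph and a less favourable stated power. No additional patients are required. The primary test should stay as it is: changing it would be a separate choice of method and would not reconcile the two sections.

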**2.11 Feasibility of Recruitment**

The study will recruit patients 328 patients over a period of 18 months from 18 Canadian and Australian pediatric and adult CF clinics. The ten participating Canadian clinics have a total clinic population of approximately 2000 patients, and the eight participating Australian clinics have a total clinic population of approximately 1500 patients. Given that at least 25-30% of the CF patient population is expected to be chronically infected with aspergillus, this would leave us with a pool of 875 Canadian and Australian patients to draw upon in order to randomize our expected sample size of 328 patients. Thus recruitment and randomization of eligible patients should be feasible. Retention of patients in the trial is not expected to be problematic since patients return to the same local CF clinic for all of their care. Our previous Canadian-Australian CF trial randomized 132 patients, and none were lost to follow-up.

**2.12/2.13 Compliance and Losses to Follow-up**

The patient’s treating physicians will be instructed not to prescribe anti-fungal antibiotics to enrolled study patients. However, if a patient’s physician insists that the patient must be started on an anti-fungal agent during the study period, then the study medication will be stopped (to avoid potential over-dosage). The patient will continue to be followed for the duration of the study period and results will be analysed according to the intention-to-treat principle. Premature discontinuation of study medication, for reasons of adverse effects or lack of efficacy, will be assessed as a secondary outcome.

Based on previous trials, we expect that 5-10% of participants will prematurely discontinue study medication but continue in the study, and that less than 5% of patients will withdraw from the study and be lost to follow-up. Losses to follow-up are rare in CF trials since patients are all followed in a central CF clinic. For instance, in our combination antibiotic susceptibility trial there were no losses to follow-up despite a 4.5 year study duration47. Patient compliance will be assessed by assessing serum itraconazole levels at 12 and 24 weeks. Patients who have detectable blood levels of itraconazole at 12 and 24 weeks will be judged to have been compliant. Patients who are non-compliant will still be included in the primary intention-to-treat analysis.

**2.14 Statistical Analysis**

*Principal Analysis of the Primary Outcome Measure:*

The final analysis will be performed with an ‘intention to treat’ approach. Patients will be included in the analysis according to the group to which they were randomized regardless of cross-over or compliance. Baseline characteristics of patients in the two treatment arms will be assessed using frequency distributions and univariate descriptive statistics including measures of central tendency and dispersion.

The principal analysis of the exacerbation proportions in the two treatment groups will be conducted using an unadjusted Fishers exact test comparing the proportion of events in the two treatment groups. A logistic regression procedure will be employed to adjust raw exacerbation proportions using important covariates that may be unbalanced at baseline that may influence outcomes (such as gender, baseline FEV1, home oxygen use, use of chronic inhaled antibiotics, use of chronic oral antibiotics, use of DNAse, use of hypertonic saline, and co-morbid illnesses).

We chose the proportion of patients having at least one exacerbation as a primary outcome measure rather than survival time to exacerbation. We believe that it is more clinically relevant to both patients and physicians to know whether or not a patient exacerbates rather than when they exacerbate. Therefore, an analysis of raw proportions followed by logistic regression procedures were chosen over log-rank tests followed by Cox proportional hazards modelling. Both alternative analytic approaches mentioned will be performed and reported.

*Principal analysis of the secondary outcome measures:* All secondary outcome measures will be analyzed using an ‘intention to treat’ analysis. Any patients who drop out of the study before the 24 week mark will have measurements of airflow obstruction, dyspnea, and quality-of-life done on the last study visit carried forward for purposes of the analysis (ie. endpoint analysis, with the last observation carried forward). Continuous outcome measures including absolute and percent changes in FEV1 and changes in the scores of the components and the total score of the CysticFibrosis Questionnaire (CFQ-R) will be analysed using multi-variate repeated measures analysis of variance using the SAS Proc Mixed program. This procedure allows us to model the covariance structure of the data and allows for missing observations. Kaplan-Meier survival curves will be used to describe the probability of remaining exacerbation-free in the two treatment arms as a function of time from randomization into the study. The curves will be compared using the log-rank test statistic. Subsequently, Cox proportional hazards modeling will be performed to adjust for other variables that are unbalanced at baseline (such as gender, baseline FEV1, home oxygen use, use of chronic inhaled antibiotics, use of chronic oral antibiotics, use of DNAse, use of hypertonic saline, and co-morbid illnesses) that could potentially affect the time to next exacerbation. The mean number of exacerbations/patient will be calculated using a weighted approach to account for each patient’s duration of follow-up in the trial. The 95% confidence interval and the P value of the rate ratio will be obtained by using Poisson regression analysis models with log transformations of the number of exacerbations and the duration of follow-up.

***Other Considerations:*** P-values will be reported as two-sided. Data will be displayed as proportions and means with 95% confidence intervals or medians with interquartile ranges as appropriate. Likewise, measures of effect, odds ratios (logistic regression) and hazards ratio (Cox proportional hazards) will be presented with 95% confidence intervals.

**2.15 Planned Subgroup Analyses:** Using the approach outlined for primary and secondary analyses, we will perform three subgroup analyses for: 1) Patients with baseline FEV1 less than 50% of predicted; 2) Patients who screen positive for ABPA (serum IgE > 1000 IU/ml and a positive IgE RAST against aspergillus); 3) Patients < 18 years of age. These analyses will primarily be hypothesis-generating in nature.

**2.16 Interim Analysis:** An independent data safety monitoring board will be appointed and the DSMB will oversee the trial, monitor adverse events, and perform an interim analysis. One interim analysis will be performed once 50% of patients have been accrued to determine if the experimental therapy is beneficial or hazardous. O’Brien-Fleming group sequential stopping rules were chosen to maintain an overall significance level of 0.05. Significance boundaries will be symmetrical with alpha = 0.005 for the interim analysis and alpha = 0.048 for the final analysis.

**2.17 Economic Issues:** A pharmaco-economic analysis evaluating the costs of this therapy will also be performed (see appendix for details). The objectives of the economic analysis will be to 1) estimate the cost of treating a CF exacerbation for the two proposed treatment strategies, 2) perform a cost minimization analysis by comparing the costs for the treatment strategies, and 3) conduct a cost-effectiveness analysis. The cost-effectiveness analysis will be assessed in terms of the cost per life year gained and QALY gained; and the analysis will be conducted from a health care system perspective. The cost assessment of treatment strategies will include only physician/clinic visit costs, hospitalization costs and drug costs since these are assumed to be the major cost drivers for treatment of CF exacerbation.

**2.18 Safety:** Itraconazole is rarely associated with liver function abnormalities and very rarely the drug can cause clinical hepatitis (3.2/100,000 prescriptions). Other potential rare side effects are hypokalemia and renal function abnormalities (occurring in less than 3% of patients). Patients will have serum electrolytes, liver function tests, and creatinine monitored regularly at 4 weeks, 12, and 24 weeks after randomization. Patients whose liver function tests increase to greater than three times above normal values, or whose creatinine increases to greater than 1.5 times baseline values, or who develop severe hypokalemia (serum potassium < 3.0) will be taken off of the study drug for the duration of the study. Patients with mild hypokalemia (serum potassium of 3.0-3.5) will be prescribed a potassium supplement and electrolytes will be monitored regularly. Further details of study monitoring for adverse events, and specific protocols and study procedures for monitoring of potential drug interactions of itraconazole with anticonvulsants, anticoagulants, oral hypoglycaemic agents, systemic and inhaled steroids, and digoxin can be found in the study appendices.

**2.19 Estimated Cost and Duration of the Trial:** 3 years; $2,257,038.00

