**2.2 The planned trial intervention**

Patients will be randomly allocated to one of two treatment arms:

1) Daily oral itraconazole for a 24 week treatment period, or

2) Identical placebo given in matched quantities of tablets for a 24 week treatment period.

Dosing of itraconazole has been calculated to provide a daily dose of approximately 5 mg/kg/d as per CF Consensus Guidelines. Itraconazole will be given in tablets containing 100 mg each once daily by mouth, unless the dose exceeds 200 mg/day, in which case it will be given twice daily.

Patients weighing 20 to 34 kg will receive 1 tablet (each tablet containing 100 mg itraconazole or placebo) once daily

Patients weighing 35 to 54 kg will receive 2 tablets (each tablet containing 100 mg itraconazole or placebo) once daily

Patients weighing 55 to 69 kg will receive 3 tablets (each tablet containing 100 mg itraconazole or placebo) divided into 2 doses (2 in the morning and one at night)

Patients weighing 70 kg or more will receive 4 tablets (each tablet containing 100 mg itraconazole or placebo) divided in two equal doses

Itraconazole or placebo will be taken after eating in the morning and in the evening. The drug will be taken with orange juice or 8 oz of a cola beverage (Coca-Cola TM) in order to maximize oral absorption. Absorption of itraconazole can be reduced in patients taking medications which suppress gastric acid production, and patients will be asked to take any prescribed proton pump inhibitors or H2-antagonists at lunchtime to avoid interference with absorption of itraconazole. All study patients will otherwise continue standard therapy for their CF as prescribed by their treating physician.

**2.3 Randomization Method:** Patients will be seen in the CF clinic after they have had their screening bloodwork and they will be reviewed to determine if they meet study eligibility criteria. Those who meet the inclusion criteria will be randomized after informed consent is obtained. The randomization process will consist of a computer-generated random listing of the two treatment allocations blocked by variable blocks of two or four and stratified by site. Randomization will be through central allocation of a randomization schedule and will be coordinated by the Ottawa Health Research Institute. Itraconazole or placebo study medications will be dispensed by the site research pharmacist according to the patient’s randomization assignment.

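### Randomisation is stratified by site, but the primary Fisher's exact test ignores site and the supporting models choose covariates by baseline imbalance: a modest loss of efficiency, not of validity

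*Protocol*

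**What the plan says.** Section 2.3 describes a computer-generated list "blocked by variable blocks of two or four and stratified by site". Section 2.11 plans recruitment "from 18 Canadian and Australian pediatric and adult CF clinics".

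For the primary outcome, Section 2.14 says: "The principal analysis of the exacerbation proportions in the two treatment groups will be conducted using an unadjusted Fishers exact test". A logistic regression then adjusts the raw proportions for "important covariates that may be unbalanced at baseline that may influence outcomes". Eight examples follow: gender, baseline FEV1, home oxygen, chronic inhaled antibiotics, chronic oral antibiotics, DNase, hypertonic saline and co-morbid illness. For time to exacerbation, the Cox model is to "adjust for other variables that are unbalanced at baseline", with the same eight examples. Both lists are open and neither names site.

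Section 2.10 sets the sample size on an absolute difference of 15 percentage points, at two-sided alpha 0.05 and 80% power: 148 per arm, raised to 328 in total for 5% non-compliance. Section 2.16 leaves alpha 0.048 for the final analysis.

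**The concern.** There are two separate matters.

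**The primary test.** Stratifying by site makes the arms alike within each clinic. If exacerbation rates differ between clinics, as they may across paediatric and adult centres in two countries, the treatment difference varies less from trial to trial than an unstratified test assumes. That test becomes conservative. Fisher's test is already conservative because it is discrete, so the two effects add up.

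**The adjusted models.** Under randomisation, baseline imbalance is chance. The gain from adjustment comes from how strongly a covariate predicts the outcome, balanced or not. A rule keyed to imbalance drops strong predictors that happen to balance. It also leaves the covariate set unknown until baseline data by arm have been seen.

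At stake are a few points of power in the primary analysis and the pre-specification of the supporting analyses.

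**Working it through.** **Inputs from the protocol.** Placebo 34% and itraconazole 34% − 15% = 19% (Section 2.10); alpha 0.05 two-sided, power 80%, 148 per arm, 328 in total (Section 2.10); final alpha 0.048 (Section 2.16); 18 sites (Section 2.11). **Assumed, because the protocol gives none:** between-site SD on the log-odds scale, site sizes and covariate strengths.

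**1. Reproduce the sample size.** With mean proportion (0.34 + 0.19)/2 = 0.265:

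n = [1.960·√(2·0.265·0.735) + 0.842·√(0.34·0.66 + 0.19·0.81)]² / 0.15² = (1.2233 + 0.5176)² / 0.0225 = 134.7, so 135 per arm.

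With the continuity correction:

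n′ = (134.7/4)·[1 + √(1 + 4/(134.7·0.15))]² = 147.7, so 148 per arm.

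This is the protocol's figure. Inflation: 296/(1 − 0.05)² = 327.98, so 328, or 164 per arm. The continuity-corrected formula approximates Fisher's test, so Sections 2.10 and 2.14 agree with each other.

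**2. Exact size and power, by enumerating all outcomes.** Size is at a common event rate of 26.5%; power is for 34% against 19%.

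| Per arm | Alpha | Fisher size | Fisher power | Pearson chi-square power |
|---|---|---|---|---|
| 148 | 0.05 | 3.7% | 80.6% | 83.8% |
| 148 | 0.048 | 3.6% | 80.1% | 83.4% |
| 164 | 0.05 | 3.8% | 84.8% | 87.4% |
| 164 | 0.048 | 3.6% | 84.2% | 87.1% |

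At 164 per arm and alpha 0.05, Fisher's discreteness costs 87.4 − 84.8 = 2.6 points.

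**3. Adding site.** Simulation with 328 patients in 18 sites of varying size, blocks of two or four within site, overall rates held at 34% and 19%, alpha 0.05 and 4,000 replicates:

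| Assumed site SD | Fisher power | Pearson power | CMH power | Fisher size | CMH size |
|---|---|---|---|---|---|
| 0 | 85.9% | 87.5% | 87.4% | 4.2% | 5.0% |
| 0.5 | 85.6% | 87.6% | 88.4% | 3.4% | 4.4% |
| 1.0 | 87.9% | 89.7% | 92.1% | 2.6% | 4.8% |

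A separate run at SD 0.6 gave CMH 89.4% against Fisher 86.9%. Simulated Fisher power can differ from the exact 84.8% through simulation error (differences of about 1 point are noise) and because the arms are not always exactly 164 each.

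**4. Splitting the gain.** Moving from Fisher to Pearson gains roughly 2 points throughout. Moving from Pearson to CMH, which is the part owed to site, gained 0.0, 0.5, 1.1 and 2.7 points at SD 0, 0.4, 0.6 and 1.0 in a run of 20,000 replicates with near-equal sites. Up to SD 0.6, most of the gain is therefore from replacing Fisher. Only at SD 1.0 does the site part become the larger.

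**5. Covariate rule.** Simulation with eight assumed prognostic covariates, two patterns of strength and 1,500 replicates:

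| Logistic model | Power | Type I error |
|---|---|---|
| Unadjusted | 87–88% | 4.1–5.9% |
| All eight, fixed in advance | 91–93% | 4.8–5.9% |
| Picked by imbalance (p < 0.2) | 88–90% | 4.1–4.5% |

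The imbalance rule keeps only part of the available gain. Applied mechanically, it does not inflate type I error.

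**The case against.** The strongest reply is that Fisher's test controls type I error, is fixed in advance and matches the sample size exactly. That stands. A reader might infer that the trial is underpowered, or that its power is marginal. The documents do not support this: Fisher's test reaches the 80% target at 148 per arm, even at alpha 0.048. If the 5% allowed for as non-compliant are assumed to lose all benefit, power at 164 per arm is 80.4% at alpha 0.05 and 79.7% at 0.048, which is essentially the target.

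A reader might also infer that the primary result cannot be reproduced from the protocol. It can: the unadjusted test is the principal analysis, and the imbalance rule touches only supporting models. Nor does that rule ignore prognosis, since Section 2.14 also requires that the covariates could influence outcome. Selecting the best of 16 covariate sets raised simulated type I error to about 6–9%, but the protocol proposes no such search.

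Odds ratios are not the only planned output either. Section 2.14 promises proportions with confidence intervals, although it names no interval for their difference.

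Closing a covariate list is often left to a statistical analysis plan. That is fair, but here the protocol itself states the principle, and a later plan that followed it would adjust by imbalance.

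Finally, sites are small: 328/18 ≈ 18 patients, and 18 × 0.265 ≈ 5 events each. Eighteen site terms in a logistic or Cox model would be sparse. This stands and shapes the fix.

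**Conclusion.** The point holds as one of efficiency and pre-specification. Size and validity of the primary test are not in question; its type I error lies below nominal, at about 3.8% by enumeration and 2.6–4.2% in the site simulations.

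At 164 per arm Fisher's power is 84.8%. A site-stratified CMH test has about 87–88% without site variation and about 89% at an assumed SD of 0.6. In the simulated comparisons the gain over Fisher runs from 87.4 − 85.9 = 1.5 points at SD 0 to 92.1 − 87.9 = 4.2 points at SD 1.0. Between 0 and about 3 points of it belong to site, and that part rests wholly on the assumed heterogeneity.

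The covariate rule gives up about 3 points in the supporting model under the assumed covariate strengths. It is worth changing because the remedy is close to free, not because the trial would fail without it.

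**What to change.** Keep 328 patients and amend Section 2.14 as follows.

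- **Primary test:** Cochran-Mantel-Haenszel stratified by site, at the interim and final alphas already stated. Pool small sites within country and clinic type (paediatric or adult), with the threshold written as a number before unblinding. One example is any site that has not filled two blocks of four (2 × 4 = 8 patients).
- **Primary estimate:** the Mantel-Haenszel risk difference with its 95% CI, because the target effect is an absolute 15 points.
- **Sensitivity analysis:** the unadjusted Fisher's exact test.
- **Supporting logistic and Cox models:** delete the condition on baseline imbalance. Name a short closed set of prognostic covariates, for example baseline FEV1, age group and chronic inhaled antibiotic use, and use it whatever the observed balance. Handle site by conditioning (logistic) or stratification (Cox), not by 18 fixed terms.

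The cost is wording, slightly more analysis work and a pooling rule to settle in advance. Site, FEV1 and age are known at randomisation, and chronic inhaled antibiotic use is already among the protocol's listed covariates, so no new data are needed.
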